## Abstract

**Abstract:**

**Introduction:**

Cleft lip and/or palate (CL/P) is a lifelong condition affecting one in 700 births. In the UK, individuals born with CL/P follow a care pathway at specialist regional cleft centres, which includes input from a range of professionals including surgeons, speech and language therapists, cleft specialist nurses, orthodontists, dentists and clinical psychologists. The cleft centres provide care from diagnosis to early adulthood. Individuals born with CL/P are typically discharged from routine care at their cleft centre between the ages of 15 and 25 years.

Outcome measures of cleft care are currently gathered at different timepoints across the treatment pathway nationally and include outcomes for speech, growth, dental health and psychosocial well-being. However, there is no consistent reporting of outcomes for young adults when they complete routine care, meaning we do not know whether variation in outcomes exists and what this might look like.

This research programme will investigate whether outcomes vary based on factors such as geographical location, biological sex, socioeconomic status or ethnicity. By understanding how outcomes might vary, and the scale and type of variation, we plan to work with young adults born with CL/P and specialist clinicians to develop ways to ensure that everyone born with CL/P in the UK receives the optimum care to meet their needs.

**Methods and analysis:**

Cleft@18–23 is an observational study of young adults born with CL/P. Recruitment is planned across all regions of the UK, beginning in April 2025 with research clinics scheduled to run between June 2025 and May 2027. The recruitment target is 640 participants born with CL/P. Participants with all cleft diagnoses, including those with additional syndromic diagnoses, will be eligible for recruitment. We will recruit participants from all ethnic and socioeconomic backgrounds. Data collection will include self-report participant questionnaires, speech samples, a hearing screen, two-dimensional and three-dimensional medical photographs, an intraoral scan and a dental assessment. A range of descriptive and inferential statistical analyses will explore variation in outcomes across different groups.

**Ethics and dissemination:**

The Cleft@18–23 study obtained ethical approval from the South West-Frenchay Research Ethics Committee on 26 November 2024 (REC reference: 24/SW/0128). Informed consent will be required for participation. Findings from the Cleft@18–23 study will be disseminated through peer-reviewed publications, conference presentations, newsletters, the study website (https://www.bristol.ac.uk/cleft18-23) and social media.

**Trial registration number:**

ISRCTN34027276.

STRENGTHS AND LIMITATIONS OF THIS STUDYFirst known dataset charting multidisciplinary outcomes at end of routine care after centralisation of cleft care in the UK.Nationwide study involving people born with all cleft subtypes including additional diagnoses.Strong collaboration with all key stakeholders including young adults with lived experience of cleft, clinicians from all professions and the charity Cleft Lip and Palate Association.Potential selection bias through difficulty reaching some underserved communities and only considers people who have had all cleft care in the UK.Ability to attend long appointments for young working adults may limit participation.

## Introduction

 Cleft lip and/or palate (CL/P) is one of the most common congenital anomalies, affecting over 1000 babies in the UK each year.^1^ People born with CL/P can experience difficulties with appearance, speech, language, hearing, dental health, facial growth and psychosocial well-being. Treatment for this population needs to be timely and accessible. Despite centralisation of cleft care in the UK over two decades ago, variation in accessing this care is reported, leading to health inequalities across different regions and socioeconomic and ethnic groups.^2 3^

Primary surgery takes place in the first year of life, with repair of a cleft lip and hard palate between 3 and 6 months of age and a repair of the soft palate between 9 and 12 months of age.^4^ On average, children born with CL/P have 3.2 admissions and spend 13.2 days in hospital in the first 2 years of life. This can range from 2.6 admissions and 9.2 days for children born with cleft lip only to 4.7 admissions and 19.7 days in children born with a bilateral cleft lip and palate.^5^ Thereafter, these children attend multiple clinical appointments with a multidisciplinary team comprising speech and language therapists, audiologists, paediatric dentists, specialist orthodontists and restorative dentists, clinical psychologists, cleft nurse specialists and surgeons for approximately 20 years. Once a young adult with CL/P has completed scheduled interventions (typically between the ages of 15 and 25 years), they transition from a care pathway facilitated via parents, structured around routine appointments and regular follow-up to a system of on-request care driven by the young person themself.

In two focus groups, 10 young adults born with CL/P aged 16–20 years reported that they found this transition in responsibility for, and ownership of care, difficult to navigate. The focus groups revealed that the transition coincides with other challenges to mental health and self-confidence as individuals start work or move away from home.^6^ The young adults added that concerns about appearance can increase in young adulthood together with worries about speech and hearing, sometimes leading to feelings of isolation.

UK cleft teams have acknowledged that variation exists in services and have suggested that outcomes for young adults born with CL/P at transition may differ between subpopulations, including those identified by equality, diversity and inclusion characteristics. Specifically, concerns about variation due to geography, ethnicity and socioeconomic status were raised. The focus group with young adults born with CL/P identified concerns that young men were less likely to access support than young women.

The Cleft@18–23 study therefore aims to be the first to investigate outcomes for young people born with CL/P after completion of routine care and explore and explain any observed variation. It will also seek to develop a tool to help all young people navigate the transition of care and access ongoing treatment and support as adults where necessary. The study programme will achieve this through four work packages. The first of these work packages (WP1) is the Cleft@18–23 research clinics. The focus of this work package is to collect data on outcomes at the end of routine care and to explore variations across regions, socioeconomic status, ethnicity, gender and biological sex. The protocol for WP1 is presented in this paper.

The WP1 protocol has been developed with input from a series of focus groups with each of the core disciplines involved in cleft care (speech and language therapists, audiologists, dentists including specialist orthodontists and restorative dentists, clinical psychologists, cleft nurse specialists and surgeons) and two focus groups with young people aged 16–20 years born with a CL/P. The protocol was further refined with input from all 16 regional centres following visits to each centre by the Chief Investigator, and by patient and public involvement (PPI) partners in this programme of work.

This study aims to answer the following primary research question: what are the levels of emotional well-being in young adults aged 18–23 years born with a CL/P and do these vary across ethnicity, biological sex, socioeconomic status and geographic location?

## Methods and analysis

### Study design and setting

The Cleft@18–23 research clinic work package is a multicentre observational study. Research clinics will take place across sites covering the 16 regional cleft units in the UK (figure 1).

**Figure 1 F1:**
[figure not shown]
Map showing locations of all UK regional cleft centres.

### Study population

Participants will be aged 18–23 years and will have been discharged from the full cleft multidisciplinary service at least 6 months prior to taking part in this study. They will no longer be receiving any active treatment that impacts outcomes such as appearance, speech and well-being but may be under review (eg, for refitting of retainers or for advice from genetic counselling). To be eligible for the study, participants must have had their primary cleft surgery in the UK before the age of 2 years and have continued their care entirely within the UK. Participants born with all cleft subtypes, including those with and without additional syndromic diagnoses, will be eligible to take part. The age group 18–23 years was chosen to ensure a sample population reflecting postcentralisation of cleft care in the UK is achieved.^7^

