### Derived variables

#### Primary outcome measure

The variable used as the primary outcome measure for this study will be derived from the SF-36.^14^ We will use the five questions of the emotional role subscale of SF-36, also known as Mental Health Inventory. SF-36 was chosen to derive the primary outcome measure following the focus groups held with young adults born with CL/P,^6^ during which it was established that emotional well-being was the primary concern while transitioning into adult care.

The Patient-Reported Outcome Measurement Information System (PROMIS)^15^ Global Health Scale will also be included. This is a standardised psychometric instrument containing 10 questions pertaining to health-related quality of life. The SF-36 emotional role subscale will remain as the primary outcome measure due to its use in calculating the power of the study and for comparison with older literature.

The decision to retain both the SF-36 and the PROMIS, which has been designed to supersede the SF-36, was driven by the desire to compare the results from this study with other studies, which were carried out prior to the development of the PROMIS and which therefore used the SF-36. However, we also want to enable future researchers to compare their results using the PROMIS with our data and using only the SF-36 would limit that ability. In order to reduce repetition within this part of the questionnaire, we limited the questions from the SF-36 to just those five which comprise the emotional role subscale, as the study was designed with these forming the primary outcome measure and the means for calculating the sample size needed to ensure a robustly powered study.

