##### Psychosocial well-being

Variables pertaining to the presence and severity of depression and anxiety will be derived from the Patient Health Questionnaire-8^18^ and the Generalised Anxiety Disorder-7.^19^ A variable measuring participants’ sociability and relationships will be derived from the Harter Self-Perception profile.^20^ A variable measuring resilience in stressful situations will be derived from the Connor-Davidson Resilience Scale-10 (CD-RISC-10), a 10-item scale derived from the 25-item CD-RISC-25, will be used to measure ability to cope with stressful life situations.^21^

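### The eligibility rule bars people in any active treatment affecting well-being, so the sample is selected on treatment status linked to the primary outcome; its scope should be limited to cleft treatment

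*Protocol article*

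**What the plan says.** The Study population section sets two conditions in succession. Participants must have been "discharged from the full cleft multidisciplinary service at least 6 months prior to taking part in this study". The next sentence adds: "They will no longer be receiving any active treatment that impacts outcomes such as appearance, speech and well-being". People under review only, for example for retainers or genetic advice, remain eligible.

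The Introduction frames the population in two ways. The general aim is to "investigate outcomes for young people born with CL/P after completion of routine care". The primary research question is broader. It asks "what are the levels of emotional well-being in young adults aged 18–23 years born with a CL/P", without restricting to people out of treatment. Its second half turns to the group contrasts, again with no such restriction: "do these vary across ethnicity, biological sex, socioeconomic status and geographic location".

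Under Primary outcome measure, the outcome is described thus: "We will use the five questions of the emotional role subscale of SF-36, also known as Mental Health Inventory". Among the secondary outcomes, "Variables pertaining to the presence and severity of depression and anxiety will be derived" from the PHQ-8 and GAD-7.

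On access to help, the Introduction reports a concern from a focus group of young adults that "young men were less likely to access support than young women". It gives no rate. It separately reports cleft teams' concerns about variation by geography, ethnicity and socioeconomic status.

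**The concern.** The second eligibility sentence names well-being, the construct of the primary outcome, and uses the word any without confining it to the cleft service. Take two discharged 20-year-olds with the same distress, one in counselling outside the cleft service and one who sought no help. As written, the first is barred and the second may enrol. Eligibility then depends on a treatment status that is likely to be related to the outcome.

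Two consequences follow, each conditional. If people in such treatment score lower on average, the sample mean is too high for the population in the primary question, and depression and anxiety will tend to look less common than they are. If uptake of treatment also differs across an exposure, the rule removes low scorers unequally and the group contrast is biased.

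The safeguards described do not reach this. The monitoring in Power calculations concerns ethnicity, sex, socioeconomic status and geography, and a sample can match on all four and still lack its treated members. The adjustment in Data analyses works on enrolled people only. The limitations box mentions underserved communities and UK-only care, but not this rule. The resource-use measure covers healthcare over the previous six months, but the article lists no item that specifically records current mental-health treatment.

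**Working it through.** **The plan's own figure.** Power calculations gives n = 600, mean 86.4 and 95% CI 84.2 to 88.6, so the half-width is (88.6 − 84.2)/2 = 2.2. No SD is printed. Inverting half-width = 1.96 × SD/√n gives SD = 2.2 × √600/1.96 = 27.5 (26.9 to 28.1 if the half-width lies between 2.15 and 2.25). Putting 27.5 back returns 84.2 to 88.6. The figure is consistent with this SD, but it is not an independent reproduction.

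**Yardsticks.** For a sex contrast with an assumed 300 v 300 split, the half-width is 1.96 × 27.5 × √(2/300) = 4.4. The difference detectable with 80% power is (1.96 + 0.84) × 27.5 × √(2/300) = 6.3.

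The documents give neither the share in treatment nor how those people score. Both are assumed below, under two models, with no true sex difference in the first.

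**Model A: treated people come from the lowest scorers.** Scores are normal with SD 27.5. The lowest fraction p is counted as distressed, and a share s of them is in treatment and excluded, so q = s × p. The distressed lie m = 27.5 × φ(z_p)/p below the overall mean. Excluding q raises a group's mean by q × m/(1 − q).

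| p | s women / men | m | Shift, women | Shift, men | Average shift | Women − men |
|---|---|---|---|---|---|---|
| 0.20 | 0.20 / 0.10 | 38.5 | 1.6 | 0.8 | 1.2 | 0.8 |
| 0.25 | 0.30 / 0.15 | 35.0 | 2.8 | 1.4 | 2.1 | 1.5 |
| 0.30 | 0.40 / 0.20 | 31.9 | 4.3 | 2.0 | 3.2 | 2.3 |

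Middle row, women: q = 0.30 × 0.25 = 0.075, and 0.075 × 35.0/0.925 = 2.8.

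**Model B: no distributional shape.** A share pF of women and pM of men is excluded, and those excluded score D points below the rest of their sex. Each sex's mean rises by share × D. With equal numbers of each sex, the overall shift is D × (pF + pM)/2 and the bias in women minus men is D × (pF − pM).

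| D | pF / pM | Overall shift | Women − men |
|---|---|---|---|
| 0 | any | 0 | 0 |
| 10 | 10% / 5% | 0.75 | 0.5 |
| 10 | 20% / 5% | 1.25 | 1.5 |
| 20 | 10% / 5% | 1.5 | 1.0 |
| 20 | 20% / 5% | 2.5 | 3.0 |
| 27.5 | 10% / 5% | 2.1 | 1.4 |
| 27.5 | 20% / 5% | 3.4 | 4.1 |
| 27.5 | 20% / 10% | 4.1 | 2.75 |

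With equal uptake, for example 5% in both sexes and D = 20, the sex contrast is unbiased but the mean still shifts by 0.05 × 20 = 1.0.

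**Reading the results.** The overall shift can match or exceed the planned half-width of 2.2, and a larger sample does not reduce it. The bias in the sex contrast stays below 4.4 throughout.

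**The case against.** The strongest reply is that the sentence means cleft treatment only. It directly follows the discharge condition, its exceptions are end-of-pathway review contacts, and clinical psychologists belong to the cleft team, so treatment affecting well-being could mean cleft psychology. Nor is the sentence redundant on that reading, since it could cover treatment by a single discipline that continues after discharge from the full team. Excluding people still in cleft treatment also follows from the aim of studying outcomes after routine care. This stands in part: the narrow reading is plausible, the article does not list the screening questions, and nothing shows that anyone has been turned away for outside mental-health care. But the words as written do not confine the exclusion to cleft care, and the primary question has no such restriction.

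Two stronger inferences are tempting and unsupported. A reader might infer that the sample is truncated on the primary outcome. It is not: there is no cut on the SF-36 score, and untreated people with low scores remain eligible. A reader might also infer that the document itself says women will be excluded more than men. It reports a focus-group concern about accessing support, with no rate and nothing about active treatment at ages 18–23. Greater exclusion of women is an inference from that concern, and greater exclusion in particular regions or ethnic groups has less behind it still.

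The magnitudes are assumption throughout. Model A places every treated person among the lowest scorers and gives treatment no effect on the score, which favours a larger bias.

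**Conclusion.** The point holds as a problem of scope with a conditional bias. The aim, the primary question and the eligibility rule do not describe the same population. Read as written, the rule selects on a treatment status related to the primary outcome, and no safeguard in the article detects or repairs it.

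Under the assumed inputs, mean well-being is overstated by roughly 1 to 3 points (4.1 in the most extreme case shown) against a planned half-width of 2.2. Women minus men is biased upward by roughly 1 to 2 points, or about 4 under more extreme inputs, which is less than the 4.4-point half-width of a 300 v 300 comparison. Both vanish if treated people score no differently, and the contrast bias also vanishes if uptake and the score gap are equal across the sexes. On the cleft-only reading, outside mental-health care does not exclude, and what remains is ambiguous wording that sites could apply inconsistently.

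**What to change.** 1. In Study population, limit the treatment exclusion to active cleft treatment under the cleft service. Keep the six-month discharge rule. State that psychological or mental-health care outside the cleft service does not exclude. This reconciles the rule with the aim and the primary question.
2. Align the Expression of Interest screening with that wording.
3. Add one item on current mental-health treatment to the first part of the questionnaire. Use it for description and for a sensitivity analysis that leaves out those in treatment. Do not use it as an adjuster: treatment status may follow from both the exposure and low well-being, so conditioning on it could bring the selection back.
4. If the broad rule has been applied since recruitment began in April 2025, record the date of change and, where possible, re-contact people turned away for this reason who left details for future opportunities.

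The cost is a minor amendment, a revised screening question and one questionnaire item. If the broad rule has already been used, the sample will mix two eligibility definitions, which is why the date of change matters. Some participants' well-being will be changing under treatment, but that belongs to the level the primary question asks about.

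If the sponsor prefers to keep the exclusion, the primary question should name the restricted population and the limitations should list this selection.

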### Power calculations

A sample of 600 would allow a mean score of 86.4 to be estimated with a 95% CI of 84.2 to 88.6 (mean and SD based on Foo *et al*^8^) for the primary outcome measure (the emotional role subscale of Short Form 36 (SF-36)). With just over 1000 babies born each year with CL/P, the total population available to recruit from over a 2-year period is approximately 7000 (1000 individuals born with cleft each year for ages 18–23—totalling 6000—plus an additional year of recruitment to include young adults who turn 18 during the first year of recruitment). The recruitment rate for a comparable study run by the same team and involving younger children was 75%^9^; therefore, recruiting 600 is achievable. Nevertheless, we propose to over-recruit by 40 (total sample size 640) as contingency for missing data.

To achieve a sample size of 640, we aim to recruit from across the UK’s cleft teams. Some serve a larger population than others, so it is likely that we may recruit more from some sites than others. Our work with young people to date suggests that they would be willing to attend this research clinic. We aim to recruit participants across all groups to ensure that the study sample reflects the general population in terms of ethnicity, socioeconomic status, gender and cleft subtypes. Recruitment will be facilitated through targeted dissemination of study information via general medical practices, dental practices and community organisations serving diverse ethnic groups. Regular evaluation of those recruited will ensure the sample is representative of target population in ethnicity, biological sex, socioeconomic status and geographic location to minimise the risk of selection bias.

### Recruitment and consent

Recruitment began in April 2025, with data collection planned to end in May 2027. Potential participants will be made aware of the study through one of six routes (figure 2). These include contact by their local cleft teams or the Cleft Lip and Palate Association (CLAPA) (https://www.clapa.com), contacting families who participated in the Cleft Care UK research project and indicated an interest in further research,^9^ and promoting the study through universities, colleges and primary healthcare providers such as dental practices and general practitioner surgeries. The study will also be promoted via social media with the help of the PPI group (see figure 2 Figure 2).

**Figure 2 F2:**
[figure not shown]
The six routes to recruitment for the Cleft@18–23 study. CLAPA, Cleft Lip and Palate Association.

Each of these routes will provide a link to the study website where more information is available and where there is an option to complete an initial ‘Expression of Interest’ contact form, which will automatically be sent to the study team. The form will help the study team determine eligibility. If a potential participant is eligible, they will be contacted by a member of the study team who has completed Good Clinical Practice training. They will explain the research clinic and go through the consent form. A link to an electronic consent form will be sent to the participant and this will be checked at the research clinic by a member of the study team. Paper consent forms will be available on request. Those who register their interest and are not eligible to take part will be directed to a form to provide their contact details if they are interested in finding out about any future opportunities.

